### Process evaluation

A process evaluation will also be undertaken to: a) assess intervention fidelity and reach; b) assess participants’ satisfaction with and acceptability of the intervention; and c) provide data to assist in interpreting the outcomes of the trial. These process evaluation questions have been developed by operationalising key elements of process evaluations (as described by Baranowski and Stables, and Linnan and Steckler (Baranowski & Stables 2000; Linnan 2002; Saunders et al. 2005)), into structured items. Data will be collected using questionnaires completed by participants, listening to a selection of the recorded telephone sessions checklists and notes kept throughout the trial by psychologists, and research notes. Descriptive statistics, Chi-square and t-tests will be used to analyse data from the process evaluation.

### Statistical analyses

The primary analysis will be by intention to treat. For both primary and secondary endpoints, linear mixed models will be used to analyse the data to account for the repeated measures (and therefore non-independent) data collected from patients. These models will enable the comparison of potential changes in patient responses over time, whether the treatment and control arms differ from each other, and whether any changes over time differ between the treatment arms (that is, whether there is a time-by-treatment interaction). Several socio-demographic variables (e.g. age, sex, income, education level, marital status) will be statistically controlled for by appropriate inclusion as covariates in the mixed models.

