### Study procedures

Figure 2 illustrates the procedures of the trial. Once consented, participants will be asked to complete a paper- or web-based baseline questionnaire, depending on their preference, approximately 6 weeks before their next 6-monthly dermatological consultation at the HRC. Once the completed baseline questionnaire is received, the participant will be randomised into either the intervention or control group. After randomisation, 3–4 weeks before their HRC appointment, the research team will send the participant the appropriate study package, including a letter describing which group they have been randomly allocated to, and the next steps in the study. In the following week, participants in the intervention arm will be contacted by telephone by the assigned psychologist to arrange a suitable time for the first intervention session, and all three sessions will be facilitated by the same psychologist.

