**Fig. 2 Fig2:**
[figure not shown]
Flow diagram

All participants will receive four study questionnaires in total; one at baseline (T0, about 6 weeks prior to their next full dermatological consultation at the HRC), one 4 weeks after their HRC consultation (which occurs soon after their third telephone session for those in the intervention group) (T1), and again 1 week after their subsequent full HRC consultation 6 months later (T2), and 12 months later (T3) (see Fig. 2). The 12 month assessment (T3) will assess longer-term effects of the intervention, but is only planned if effectiveness of the intervention is demonstrated at 6 months. Participants who do not complete and return the study questionnaires in the specified time period will be contacted by the research team via telephone or email, as a reminder about the study.

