### Effect evaluation

Table 2 provides an overview of the measures of efficacy, economic evaluation, and timing of measurement.

**Table 2 Tab2:** Measures and timing of assessment in the Melanoma care study

Variables	Measures	Baseline (T0)	T1^*^	T2^Φ^	T3^‡^
Fear of new or recurrent melanoma	Fear of Cancer Recurrence Inventory	✓	✓	✓	✓
Depression, anxiety, stress and depression	Depression Anxiety and Stress Scales (DASS-21)	✓	✓	✓	✓
Health related quality of life	AQOL-8D and FACT-M	✓		✓	✓
Knowledge	A 9 item scale specifically developed for this study	✓	✓	✓	✓
Healthy behavioural adjustment to melanoma risk	The Sun Protection Habits Scale (SPHS) and adapted items for sun protection and skin self examination	✓		✓	✓
Satisfaction with clinical care	Consultation Satisfaction Questionnaire (CSQ)	✓	✓	✓	
Unmet information and support needs	Modified Cancer Survivors’ Unmet Needs (CaSUN)	✓	✓	✓	
Resource use and cost outcomes	Items developed for this study (resource use) and Medicare data (PBS and MBS)	✓		✓	✓
Health literacy		✓			
Medical record	From the melanoma clinics’ databases	✓		✓	✓
Process evaluation	Developed for use in this study.	✓		✓	
Demographic and other risk factors	Age, gender, marital status, number of children, education, income, occupation	✓			

^*^T1: 6 weeks after randomisation, ^Φ^T2: 7 months after randomisation, ^‡^T3: 13 months after randomisation

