#### Secondary outcome measures

*General depression, anxiety and stress*: measured using the short version of the Depression Anxiety and Stress Scales (DASS-21) (Lovibond & Lovibond 1995). The DASS-21 is a set of three 7-item self-report scales designed to measure the emotional states of depression, anxiety and stress. The total score of each subscale of the DASS-21 is classified from “normal” to “extremely severe”.

*Health-related quality of life (HRQoL)*: HRQoL will be assessed using two measures. The Assessment of Quality of Life—8 Dimensions (AQoL-8D) is a 35-item health-related QoL preference-based measure, specifically developed for mental health, with norms for the Australian population by age and sex. The AQOL-8D produces utilities for quality-adjusted life year (QALY) estimation, used in economic evaluations (Richardson et al. 2009; Richardson & Iezzi 2010). The Functional Assessment of Cancer Therapy (FACT-M) (Cormier et al. 2005) (melanoma) contains the 27 core items of the FACT–G (general), plus an additional 24 melanoma-specific items encompassing three domains: physical well-being (20 items), emotional well-being (3 items), and social well-being (1 item). The FACT-M yields both a total QoL score as well as domain scores. An algorithm is available to transform FACT-M scores to utilities for QALY estimation, thereby facilitating a comparison of health economic outcomes.

*Behavioural adjustment to melanoma risk*: Three melanoma-related behaviours will be assessed: sun exposure, sun protection, and skin self-examination. Three items from the consensus-based set of core survey items developed by Glanz et al. will be used to assess sun exposure (Glanz et al. 2008). One item will assess instances of sunburn in the past 12 months. The Sun Protection Habits Scale (Glanz et al. 2002) will be adapted to assess the use of seven sun protection behaviours (e.g. sunscreen use). Engagement in skin self-examination will be assessed with three items adapted from Manne et al. (Manne & Lessin 2006).

*Satisfaction with clinical care*: will be measured using the Consultation Satisfaction Questionnaire (CSQ) (Baker 1990). The CSQ is comprised of 18 items assessing: general satisfaction (3 items); professional care (7 items); depth of relationship (5 items); and perceived time (3 items).

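### Sun exposure and sun protection are assessed about 33 weeks apart, and no calendar term is named among the covariates: change over time may be confounded with season, and the arm comparison may carry removable noise

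*Protocol article*

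**What the plan says.** Under Secondary outcome measures, the protocol article says of behavioural adjustment: "Three melanoma-related behaviours will be assessed: sun exposure, sun protection, and skin self-examination". Table 2 lists the instruments as "The Sun Protection Habits Scale (SPHS) and adapted items for sun protection and skin self examination" and schedules them at T0, T2 and T3, not at T1. T3 takes place only if the intervention is shown to work at 6 months.

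The timing is given under Study procedures. There is "one at baseline (T0, about 6 weeks prior to their next full dermatological consultation at the HRC", and the T2 questionnaire comes "again 1 week after their subsequent full HRC consultation 6 months later (T2". The Table 2 footnote adds "T2: 7 months after randomisation".

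The Statistical analyses section uses one linear mixed model for primary and secondary endpoints alike. It lists three questions for that model: change over time, difference between arms, and their interaction ("These models will enable the comparison of potential changes in patient responses over time, whether the treatment and control arms differ from each other" covers the first two). The adjustment variables it names are socio-demographic, given as examples. The Covariates section adds clinical items from the clinic records. Neither section mentions season or date of assessment. Randomisation uses minimisation, with clinic site the only factor named.

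One behavioural item has a stated recall period: "One item will assess instances of sunburn in the past 12 months". The article gives none for the other sun items.

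**The concern.** Time outdoors and the use of sun protection plausibly vary with the time of year. If the questions ask about current or recent behaviour, a participant who answers at T0 in summer answers at T2 well outside summer, and the reverse. Time since baseline and calendar time then move together within each person.

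Two things are at stake, both confined to these secondary outcomes. First, change over time, which the model is meant to describe, may partly be a change of season. Second, if participants enter at different times of year, season adds variance at each assessment. It also weakens baseline as a predictor of T2, because the seasonal parts at the two assessments tend to run in opposite directions. A calendar term would remove that variance.

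**Working it through.** **Interval.** First, the article's own figure. The study package goes out "After randomisation, 3–4 weeks before their HRC appointment". Taking that as the time of randomisation and 30.44 days per month, randomisation to T2 is 6 months plus 4 to 5 weeks (28 to 35 days), or 6.92 to 7.15 months. This agrees with the 7 months in the Table 2 footnote.

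T0 to T2 is 6 weeks + 6 months + 1 week = 6 + 49/30.44 = 7.61 months (6 + 26 + 1 = 33 weeks).

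**Seasonal phase.** Model season as a 12-month cosine of amplitude A.
- Phase shift φ = 360° × 7.61/12 = 228°.
- Correlation of the seasonal parts at T0 and T2, with entry spread over the year: cos φ = -0.67 (-0.665 before rounding).
- Largest seasonal difference between T0 and T2, as a share of peak-to-trough: |sin(φ/2)| = 0.91.
- Distance from the same point of the year: 12 - 7.61 = 4.39 months, where exact opposition would be 6. The seasons are quite different but not fully opposed.

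**Assumptions, none of them in the document.** A = 0.25 to 0.5 non-seasonal SD; non-seasonal variance 1; non-seasonal T0-T2 correlation 0.5; entry at one time, over 6 months or over 12 months. The 64 per arm is the article's figure before attrition.

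**Precision of the baseline-adjusted arm difference.** Let s be the seasonal variance. Then the variance at each time is v = 1 + s, the covariance is c = 0.5 + s·cos φ, and the residual variance is v - c²/v. Without season it is 1 - 0.25 = 0.75.

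- Entry spread over 12 months, s = A²/2.
  - A = 0.5: s = 0.125, v = 1.125, c = 0.417, residual 0.9705. Ratio 0.9705/0.75 = 1.294; SE ratio √1.294 = 1.14.
  - A = 0.25: s = 0.03125, v = 1.03125, c = 0.479, residual 0.8086. Ratio 1.078; SE ratio 1.04.
- Entry over 6 months, averaged over possible start dates: variance ratios 1.047 and 1.178; SE ratios 1.02 and 1.09.
- Entry at one time of year: s = 0, ratio 1.00.

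| Entry | Variance ratio (A = 0.25, 0.5) | SE increase | Power at d = 0.5, 64 per arm (0.904 without season) |
|---|---|---|---|
| one time | 1.00, 1.00 | none | 0.904 |
| 6 months | 1.047, 1.178 | 2-9% | 0.891, 0.853 |
| 12 months | 1.078, 1.294 | 4-14% | 0.882, 0.819 |

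The assumed correlation matters. With A = 0.5, 12-month entry and a correlation of 0.7, the SE ratio is 1.24.

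**Simulation check** (4,000 trials, A = 0.5, 64 per arm). With 12-month entry the SE is 0.177 without calendar terms and 0.156 with them; with one 6-month window, 0.169 and 0.155. Mean bias without calendar terms is -0.003 and 0.004, that is, none.

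**Cohort-wide T0-T2 shift from season alone.** With entry at one time, the maximum is 2A × 0.912 = 0.46 to 0.91 SD. A six-month window shrinks this by sin(90°)/(π/2) = 0.637, to at most 0.29 to 0.58 SD; depending on the start date it can be zero. With even entry over 12 months it is zero.

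The two effects therefore trade off: the mean shift is largest when entry is concentrated, and the precision loss is largest when entry is spread.

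**The case against.** The strongest reply is that this is a covariate choice for some of many secondary outcomes, in a condensed article whose adjustment list is openly illustrative. An analysis plan that is not shown could add season. That stands as a limit: the article names no calendar term, but it does not follow that none will be used. It does not dispose of the point. The examples given are of socio-demographic variables, season is not one, and the article applies a single model to outcomes for which this spacing matters.

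A reader might infer that the arm comparison is biased, or that the trial's conclusions on sun behaviour would be seasonal artefacts. The document does not support this. Randomisation gives both arms the same calendar spread in expectation, and the model's time effect absorbs any shift common to both arms. The hypotheses under Study aims and hypotheses are stated against usual care, and nowhere does the article say that within-arm change will be read as an effect of the intervention.

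A reader might also infer that observed change in these outcomes would be mainly seasonal. That depends on amplitude, item wording and entry pattern, none of which is given. The sunburn item spans a full year at both assessments and falls outside the concern. If the other items refer to a named season, little or nothing remains.

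On entry pattern, Recruitment procedures describes a bulk mailing to patients seen at least every six months, which makes roughly six-month entry plausible. The length of recruitment is not stated, so this is an inference.

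**Conclusion.** The point holds as a minor improvement to secondary outcomes. The interval of about 33 weeks follows from the article, as does the absence of a calendar term among the covariates it names. If the sun exposure and sun protection items capture current or recent behaviour, T0-T2 change in them may be confounded with season, and the arm comparison may be less precise than it need be.

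Under the assumed amplitude of 0.25-0.5 SD and correlation of 0.5, the loss is about 2-9% in SE with six-month entry and 4-14% with entry over a year. It is nil with entry at a single time of year or with items tied to a fixed season. The randomised contrast remains unbiased, and the FCRI primary outcome is not touched.

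**What to change.** For the sun exposure and sun protection outcomes, leaving out the 12-month sunburn item, add the calendar date of each assessment to the mixed model as sine and cosine terms, or as season at each assessment. State that conclusions on these outcomes rest on the between-arm contrast at T2, and that within-arm T0-T2 change will not be interpreted as an effect. The second statement is still needed if entry is concentrated in a few months: calendar date is then nearly collinear with the time effect, and no adjustment can separate the two within an arm.

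The sine and cosine pair costs two degrees of freedom and needs questionnaire dates. The article implies that dates are tracked, since randomisation follows receipt of the baseline questionnaire and late responders are reminded, but it does not say that they are recorded. That should be confirmed.

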### Recruitment procedures

Individuals who meet the eligibility criteria will be recruited from melanoma high risk clinics (HRC) across New South Wales, Australia. These clinics provide a specialised clinical management service for people at very high risk of developing further primary melanoma (Moloney et al. 2014). This includes patients ≥18 years of age who belong to one or more of the following groups:Personal history of ≥1 invasive melanoma and dysplastic nevus syndrome; orPersonal history of ≥2 primary invasive melanomas, with at least one occurring in the 10 years prior to study recruitment; orPersonal history of ≥1 invasive melanoma and a family history of at least three first- or second-degree relatives with a confirmed history of melanoma; orConfirmed carrier of a *CDKN2A* or *CDK4* gene mutation (the highest penetrance susceptibility gene mutations for melanoma). No history of invasive melanoma is required for this group.

The first HRC was established in 2006 at the Sydney Melanoma Diagnostic Centre at the Royal Prince Alfred Hospital in metropolitan Sydney. In 2012, the service expanded to include clinics at the Melanoma Institute Australia in metropolitan Sydney and the Newcastle Skin Check Clinic in a regional, coastal area; all three of these clinics were sources of recruitment for this study. In late 2014, another HRC opened at Westmead Hospital in metropolitan Sydney. Participants attend these clinics at least 6-monthly for skin monitoring via a variety of clinical imaging techniques, including dermoscopy, digital dermoscopy and total body photography. Individuals are managed according to the assessment of any lesions detected (Moloney et al. 2014). Education in skin self-examination techniques is also provided where appropriate and a record of skin self-examination is maintained by the individual.

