### Randomisation

Randomisation will be performed ensuring allocation concealment using the telephone randomisation service at the National Health and Medical Research Council of Australia (NHMRC) Clinical Trials Centre, The University of Sydney. Recruited participants will be assigned an ID code and randomised using minimisation, stratified by HRC site.

To minimise potential contamination, no components of the intervention will be made available to patients other than those in the intervention group until after all data have been collected and the trial is completed. Some of the HRC clinicians have been involved in developing and reviewing intervention components, but they will not be provided with a personal copy and will be asked not to initiate conversation specifically about the intervention with their patients. For ethical reasons, we cannot preclude clinician communication with ‘control’ participants about topics covered by the intervention. Indeed this may happen regardless of the trial due to education from other sources; however, time constraints in the clinic setting are highly likely to minimise contamination among controls.

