#### Covariates

Information on demographic factors including age, sex, marital status, education, number of children, health literacy and total family income will be collected. In addition, clinical information such as their doctor’s name, presence of dysplastic nevus syndrome, presence of high penetrance genetic mutation, family history of melanoma, dates of personal melanoma diagnoses, melanoma American Joint Committee on Cancer (AJCC) stage, Breslow thickness, site of the melanoma(s), and other major illnesses will be extracted from the clinic records.

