### Sample size

Sample size calculation has been based on 80 % power and a two-sided α = 0.05 test. Because there is no existing literature or clinical opinion to provide an estimate of the minimal clinically important difference, a standardised mean difference (Cohen’s *d*) of 0.5 was employed, which is a moderate effect size and has been found to be applicable to a wide variety of patient-reported outcomes (Norman et al. 2003). Based on these values, the sample size required is 64 per group. When taking into account the expected attrition rate of 20 %, the sample size required is 77 per group (154 total).

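### Randomisation is stratified by clinic, but the analysis model does not name clinic; between-arm tests at T2 are then slightly conservative if clinic predicts outcome

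*Protocol article*

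**What the plan says.** Under Randomisation, participants are "randomised using minimisation, stratified by HRC site". No other minimisation factor is named. Under Recruitment procedures, two clinics in metropolitan Sydney and one in a regional coastal area are described, and "all three of these clinics were sources of recruitment for this study".

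Under Statistical analyses, for primary and secondary endpoints alike, "linear mixed models will be used to analyse the data to account for the repeated measures". The models are meant to address change over time, difference between arms, and the time-by-treatment interaction. Adjustment is described in one sentence: "Several socio-demographic variables (e.g. age, sex, income, education level, marital status) will be statistically controlled for by appropriate inclusion as covariates". Clinic is not mentioned.

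The Covariates section says that "age, sex, marital status, education, number of children, health literacy and total family income will be collected". It adds items taken from clinic records, including the treating doctor's name and features of the melanoma. HRC site is not listed there either. Under Outcome measures, the primary outcome is tied to the T2 questionnaire at 6 months.

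**The concern.** When allocation is balanced within clinics, variation between clinics cannot contribute to the difference between arms. A model without clinic still counts that variation as residual noise, so the standard error it reports exceeds the true sampling variability of the treatment estimate. Intervals are too wide, the test rejects less often than its nominal level, and some power is given away. The usual remedy is to analyse by the factors used in the randomisation.

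The article does say which kind of variable will be adjusted for. It chooses socio-demographic characteristics, a class to which clinic does not belong, and leaves out the only factor that the allocation is said to control. Because one model description serves all endpoints, it also covers outcomes where clinic could well matter. Sun exposure and sun protection may differ between a coastal and a metropolitan setting, and the Consultation Satisfaction Questionnaire rates clinical care itself.

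**Working it through.** **Inputs from the article.** Three recruiting clinics; 1:1 allocation balanced by site; d = 0.5; two-sided α = 0.05; 80% power; 64 evaluable per group.

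**Inputs assumed, because the article gives none.** Share of T2 outcome variance due to site, R² = 0 to 20%. For the simulation, evaluable site sizes of 60, 44 and 24 (total 128).

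**Step 1: the plan's own figure.** n per group = 2(1.96 + 0.842)²/0.5² = 62.8, or 63 by the normal approximation. The two-sample t-test gives 63.8, rounded up to 64. The stated 64 per group reproduces.

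**Step 2: standard error at a single time point.** With total variance 1 and balance within site, the true variance of the difference in means is (2/n)(1 − R²). The model without site estimates 2/n. The ratio of reported to true standard error is 1/√(1 − R²):
- R² = 5%: 1/√0.95 = 1.026
- R² = 10%: 1/√0.90 = 1.054

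**Step 3: type I error.** True level = 2[1 − Φ(1.96/√(1 − R²))]:
- R² = 5%: 2[1 − Φ(2.011)] = 0.044
- R² = 10%: 2[1 − Φ(2.066)] = 0.039

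**Step 4: power at d = 0.5, R² = 10%, n = 64.** The reported standard error is √(2/64) = 0.1768 and the true one is 0.1768 × √0.90 = 0.1677.
- Without site: Φ[(0.5 − 1.96 × 0.1768)/0.1677] = Φ(0.915) = 0.82
- With site: Φ(0.5/0.1677 − 1.96) = Φ(1.02) = 0.85

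**Step 5: simulation.** 8,000 runs per setting, linear model at one time point, allocation balanced within site. Simulation error on a 5% rate is √(0.05 × 0.95/8000) = 0.24 percentage points.

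| Site share of variance (assumed) | Type I error, site omitted | Type I error, site included | Power, site omitted | Power, site included |
|---|---|---|---|---|
| 0% | 0.048 | 0.049 | 0.80 | 0.80 |
| 1% | 0.047 | 0.048 | 0.80 | 0.80 |
| 5% | 0.045 | 0.051 | 0.80 | 0.82 |
| 10% | 0.038 | 0.049 | 0.82 | 0.84 |
| 20% | 0.026 | 0.046 | 0.83 | 0.89 |

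The simulation agrees with the formulas. Power without site does not fall as R² rises, because total variance is held at 1. The loss is the gap between the last two columns.

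**Step 6: the time-by-treatment reading.** For one participant, the change from T0 to T2 subtracts any clinic effect that is the same at both visits. A clinic effect stable over time therefore drops out of a within-patient contrast. A second simulation used 154 participants, three sites balanced within site, 20% missing at T2, an assumed within-patient correlation of 0.6, and a random-intercept model without site (400 runs per setting). Type I error for the T2 interaction term was 0.048 at each of R² = 0, 10% and 20%, and the model standard error was 1.02 times the empirical one each time. Simulation error here is √(0.05 × 0.95/400) = 1.1 points, so this supports the algebra but would not detect a small departure. With the same 20% loss, a T2-only comparison over 8,000 runs gave 0.049, 0.041 and 0.031. The conservatism remains but is slightly milder than in the table, as expected when attrition partly undoes the balance.

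**The case against.** The strongest reply is that the size of the problem depends on which contrast carries the conclusion. The plan is a repeated-measures model with a time-by-treatment term, and step 6 shows that stable clinic effects cancel there. This stands, and it limits the point. It does not remove it, because the article ties the primary outcome to T2 and also lists a plain comparison between arms, without saying which term is the test.

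Second, the covariate list is illustrative and this is a condensed article, so the final list could sit in an analysis plan that is not shown. That is fair, and nothing in the article excludes site. But the examples are open only within the socio-demographic class, and the Covariates section, which is broader and includes the treating doctor's name, still does not list clinic.

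Third, the three clinics provide the same kind of service, and the article gives no reason to expect a clinic effect on FCRI severity. This also stands: for the primary outcome the effect may be negligible.

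Two stronger readings are tempting, and the article supports neither. A reader might infer that the omission makes the standard errors wrong in a way that threatens false-positive findings. The error runs the other way, and only if clinic predicts outcome. A reader might also infer that adjusting for income will delete participants who leave it blank and so undermine intention to treat. The article states no complete-case rule and no rate of missing income. Handling of missing covariates is ordinary analysis-plan content, so no such loss can be claimed.

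**Conclusion.** The mismatch between randomisation and the described analysis is real, and its consequence is modest. Where a between-arm contrast at T2 is used and site explains 5% or 10% of outcome variance, type I error is about 4.5% or 3.8%, the standard error is about 3% or 6% too large, and power is lower by roughly one to three points. Those variance shares are assumptions, since the article gives no site effect. There is no effect if site is not prognostic, and little or none under a within-patient contrast with stable site effects. The direction is conservative throughout. The secondary outcomes on sun behaviour and satisfaction with care are the likelier places for it to matter. It is worth correcting because the correction is nearly free, not because the primary conclusion is in danger.

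**What to change.** Add one sentence to Statistical analyses stating that HRC site, and any other factor used in the minimisation, enters every primary and secondary model as a fixed effect alongside the socio-demographic covariates. List site in the Covariates section as well.

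The cost is that sentence and two degrees of freedom (three clinics less one). Site is known for every participant, so nobody is lost, and the sample size does not change.

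Baseline adjustment is a separate choice and is not needed to repair this point. If the baseline value of the outcome is used as a covariate, T0 must be taken out of the response vector so that it is not counted twice.
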